##### Screen-positive participants

We will collect spontaneously voided urine and spot sputum specimens (induced, if necessary) from all screen-positive participants (POC CRP ≥8 mg/L in the intervention arm; presence of ≥1 symptom in the control arm) for urine LAM (Alere Determine TB-LAM) and sputum Xpert Ultra testing. In accordance with current WHO guidelines, sputum Xpert Ultra testing will be performed if (1) urine LAM is negative or (2) urine LAM is positive and the participant has risk factors for drug-resistant TB (prior TB treatment, contact with drug-resistant TB case). Participants who test positive for TB by urine LAM and/or sputum Xpert Ultra will be referred to clinicians for TB treatment initiation. To maximize real-world relevance, sputum will not be submitted for mycobacterial culture because most HIV programs in high burden countries use Xpert (standard cartridge or Ultra) as the confirmatory test for TB. Participants who screen-positive but test negative by urine LAM and sputum Xpert Ultra will not be given 3HP at the time of enrollment (as their risk of active TB remains non-negligible), but will be eligible for TPT initiation at the discretion of treating (non-study) clinicians throughout the follow-up period.

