### Outcomes

The primary trial endpoint is a composite outcome of microbiologically confirmed incident TB and all-cause mortality, measured as time to first diagnosis of incident TB or death from any cause. Microbiologically confirmed incident TB is defined as active TB diagnosed by either culture, one non-trace positive Xpert Ultra result or two trace-positive Xpert Ultra results, or positive urine LAM result from 3 months after randomization to the end of follow-up (at 2 years, or at the time of last contact for participants who are lost to follow-up). To assess active TB status at the end of follow-up, 2 spot sputum specimens will be collected from all participants who have not taken anti-TB treatment during the study at the final (24 months) study visit for sputum Xpert Ultra testing, liquid culture, and drug susceptibility testing (for participants who received any TPT). Secondary outcomes are presented in Table 2.

**Table 2 Tab2:** Secondary outcomes of the TB SCRIPT trial

Outcome	Numerator	Denominator

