### Blinding

TB SCRIPT is a single-blinded trial. We will not be blinded to intervention allocation, as we will perform baseline TB screening and subsequent procedures based on the results of screening (e.g., 3HP initiation for eligible screen-negative participants). Participants and routine clinic staff will be blinded, as will the study principal investigators (except for the trial statistician). To facilitate blinding, all participants will undergo a finger prick and have capillary blood measured for CRP (intervention) or beta-human chorionic gonadotropin (β-hCG; control, regardless of gender). POC CRP and β-hCG assays will be provided by BodiTech, Med Inc. and measured using the iCHROMA Reader which provides analysis of more than 30 unique markers, including CRP and β-hCG. There are no procedures for unblinding, as clinicians are free to order TB testing, initiate TB treatment, or initiate TPT for study participants at any time.

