#### Final TB status assessment

For all participants who have not taken anti-TB treatment during follow-up, we will collect 2 spot sputum specimens at the final (24 months) study visit for sputum Xpert Ultra testing; repeat Xpert Ultra testing, if the initial test is trace-positive; and liquid culture and drug susceptibility testing (DST). Speciation testing will be performed on all positive cultures to confirm the presence of *M. tuberculosis* complex using Ziehl-Neelsen smear microscopy for detection of acid-fast bacilli and SD MPT64 (Standard Diagnostics Bioline TB Ag MPT64, South Korea) for rapid *M. tuberculosis* antigen detection. DST will include susceptibility testing to all first-line TB medications including isoniazid and rifamycin-based drugs. Participants will be classified as having incident TB if at least one of the following criteria are met: at least one sputum culture positive for *M. tuberculosis* complex, one non-trace-positive Xpert Ultra result, or two trace-positive Xpert Ultra results.

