### Statistical methods

#### Primary and secondary outcomes

The primary trial outcome is a 2-year composite endpoint of microbiologically confirmed incident TB and all-cause mortality, measured as time to first diagnosis of incident TB or death from any cause. The primary analysis will be by intention-to-treat (ITT), including all participants randomized without regard to the results of baseline TB screening, and we will use a two-sided alpha (0.05 significance) in assessing the effect of the intervention on the primary outcome. Participants with prevalent TB will be included in the analysis to preserve the randomized groups (the ITT principle) but excluded from the outcome of incident TB because subsequent disease is more likely to represent relapse or failure (and these participants will not routinely receive TPT). Time from randomization to first event (diagnosis of incident TB or death from any cause) will be analyzed using the log rank test and Cox proportional hazards models, adjusted for the study site. If data are missing or a patient is lost to follow-up, a patient’s data will be censored in the analysis at the date of last known contact. We will also use the Mantel-Haenszel method to determine standardized incidence rates and incidence rate differences. Balance at baseline on all known and suspected prognostic factors will be assessed, and if important imbalances are found (e.g., differences in median baseline CD4 count), a sensitivity analysis will be conducted using a Cox model to adjust for these factors. We will also assess the impact of clinician-initiated co-interventions (e.g., clinician-initiated TPT, clinician-initiated TB treatment) on the primary outcome. We will conduct a sensitivity analysis in which these participants are censored as soon as they are initiated on TPT or TB treatment by non-study clinicians. Standard checks for variation by enrollment site will also be planned. Secondary outcomes for the primary objective include the individual primary endpoints (TB incidence and mortality analyzed separately) and 2-year isoniazid-resistant TB incidence and will be analyzed using a similar approach; there will be no adjustment for multiplicity since these are pre-specified secondary outcomes.

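### The co-intervention sensitivity analysis censors at clinician-started TB treatment as if it were the same as preventive therapy, and no stated analysis shows whether the result depends on TB treated without confirmation

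*Protocol article*

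**What the plan says.** The primary endpoint (Protocol article, Outcomes) reads: "composite outcome of microbiologically confirmed incident TB and all-cause mortality, measured as time to first diagnosis of incident TB or death from any cause". Incident TB is "active TB diagnosed by either culture, one non-trace positive Xpert Ultra result or two trace-positive Xpert Ultra results, or positive urine LAM result", counted from 3 months after randomization. Starting TB treatment is not a criterion.

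Under Blinding, "clinicians are free to order TB testing, initiate TB treatment, or initiate TPT for study participants at any time"; no confirmation is required. Under Screen-positive participants, those with a positive study test "will be referred to clinicians for TB treatment initiation", so routine clinicians also start treatment for TB that the study itself finds. Those who screen positive but test negative get no study 3HP at enrollment, "but will be eligible for TPT initiation at the discretion of treating (non-study) clinicians throughout the follow-up period".

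The 24-month test is restricted: "2 spot sputum specimens will be collected from all participants who have not taken anti-TB treatment during the study" (Outcomes). The section Final TB status assessment sets the same limit: "For all participants who have not taken anti-TB treatment during follow-up, we will collect 2 spot sputum specimens at the final (24 months) study visit".

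Under Statistical methods (Primary and secondary outcomes), participants with prevalent TB stay in the intention-to-treat analysis but cannot contribute incident TB. The impact of clinician-initiated TPT and TB treatment is to be assessed, and the one method named is a sensitivity analysis in which "these participants are censored as soon as they are initiated on TPT or TB treatment by non-study clinicians".

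**The concern.** Censoring in a Cox or log-rank analysis assumes that those censored carry the same later risk as comparable participants still under observation. That is hard to defend at the start of TB treatment, which happens because TB is suspected. The rule takes people out when their chance of having the outcome is probably at its highest, and it stops counting their deaths.

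Two further features add to this. Routine clinicians start all TB treatment, so nothing in the wording clearly exempts treatment that follows a positive baseline test. Taken that way, the analysis would remove near baseline the prevalent cases that the primary analysis retains to preserve randomization. And a participant treated after month 3 without a positive test has no TB event on record and is not tested at month 24.

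What is at stake is the robustness claim. If unconfirmed TB were more often treated in one arm, the primary hazard ratio would shift, and the analysis meant to examine co-interventions would not reveal it.

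**Working it through.** **1. The plan's own figure.** Inputs from Sample size: 860 per arm, 12% loss, control mortality 5.2% and TB incidence 7.3% (sum 12.5%), 35% relative reduction, two-sided 0.05.

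- n = 860 × 0.88 = 756.8 per arm; p0 = 0.125; p1 = 0.65 × 0.125 = 0.08125
- Expected events: 94.6 and 61.5 (plan: 95 and 62)
- Power = Φ{[|p0 − p1|√n − 1.96√(2p̄(1 − p̄))] / √(p0(1 − p0) + p1(1 − p1))} = Φ{(1.204 − 0.843)/0.429} = Φ(0.84) = 0.80

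The stated 80% reproduces.

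**2. Where unconfirmed TB appears.**

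| Place | Treatment of confirmed TB | Treatment without confirmation, after month 3 |
|---|---|---|
| Primary endpoint | Event at diagnosis, if from month 3 | Not an event; a later death or routine positive test is |
| 24-month sputum | Not collected | Not collected |
| Table 2 | Incident or prevalent TB | No incident TB outcome; treatment whatever the Xpert result is counted only up to 3 months |
| Adjudication (Oversight and monitoring) | Deaths only | Deaths only |
| Co-intervention analysis | Unclear whether exempt | Censored, later deaths lost |

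**3. Effect on the endpoint as written.** The article gives no rate of unconfirmed treatment, so let f0 (control) and f1 (CRP) be the assumed shares of incident TB treated without confirmation. With TB and death added as in the plan:

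- p0 = 0.052 + 0.073(1 − f0)
- p1 = 0.65 × [0.052 + 0.073(1 − f1)]

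| f0 / f1 | p0 | p1 | Risk ratio | Events | Power |
|---|---|---|---|---|---|
| 0 / 0 | 12.5% | 8.1% | 0.65 | 156 | 0.80 |
| 10% / 10% | 11.8% | 7.7% | 0.65 | 147 | 0.77 |
| 20% / 20% | 11.0% | 7.2% | 0.65 | 138 | 0.74 |
| 30% / 30% | 10.3% | 6.7% | 0.65 | 129 | 0.71 |
| 40% / 40% | 9.6% | 6.2% | 0.65 | 120 | 0.68 |
| 20% / 10% | 11.0% | 7.7% | 0.69 | 141 | 0.62 |
| 30% / 15% | 10.3% | 7.4% | 0.72 | 134 | 0.51 |
| 40% / 20% | 9.6% | 7.2% | 0.75 | 127 | 0.39 |
| 15% / 30% | 11.4% | 6.7% | 0.59 | 137 | 0.89 |

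Equal shares cost power only. Unequal shares move the estimate, in either direction.

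**4. Effect of the censoring rule.** Simulation with 1,000,000 per arm and exponential times to TB and to death matched to the planned 2-year risks. It adds an assumed share of deaths preceded by unconfirmed treatment, started 0.1 year before death. The hazard ratio is the ratio of event rates per person-time.

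| Incident TB unconfirmed (control / CRP) | Deaths preceded by treatment | All TB counted | As written | Planned censoring | Treatment counted as event |
|---|---|---|---|---|---|
| 30% / 30% | 20% / 20% | 0.64 | 0.64 | 0.64 | 0.64 |
| 30% / 15% | 20% / 10% | 0.64 | 0.71 | 0.75 | 0.64 |
| 15% / 30% | 10% / 20% | 0.64 | 0.58 | 0.55 | 0.64 |

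With unequal shares the censoring analysis lies further from 0.64 than the primary analysis does, because it also drops deaths after treatment. The last column returns to 0.64 partly by construction: the simulation includes no one treated for TB who neither has TB nor dies.

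**5. Censoring at clinician-started TPT.** Simulated under no true effect, assuming 85% (control) and 45% (CRP) screen positive and 20–40% of them receive TPT. These percentages are assumptions; 85% and 45% are the complements of the planned 3HP initiation (15% and 55%), which is not the same as screen-positivity. Ratio of the censored to the uncensored hazard ratio:

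- TPT given preferentially to lower-risk patients: about 0.93–0.99, depending on timing
- No selection by risk: about 1.00
- Preferentially to higher-risk patients: about 1.01–1.09

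**The case against.** **The primary analysis does not depend on this rule.** That is right. A confirmed-only endpoint is a deliberate choice. A reader might infer that a participant treated empirically can never contribute an event, but a later death or routine positive test still counts. Table 2 also includes deaths from probable TB.

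**The missing 24-month sputum loses little.** Largely true: testing at 24 months would not recover cases already treated. The restriction matters only because it leaves treatment records as the main trace of unconfirmed TB.

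**Treatment after a positive study test is the trial's own pathway, not a co-intervention.** This may well be the intent. The text does not prove that every treated prevalent case would be censored; it only permits that reading. One might go further and compute lost deaths: assuming 10% prevalent TB and 15% mortality among them, 0.10 × 0.15 = 1.5 percentage points, or 29% of the planned 5.2% (10–58% over prevalences of 5–15% and mortalities of 10–20%). Neither rate is in the article, which expects similar prevalent TB detection in the two arms. The figure describes lost events, not bias in the hazard ratio.

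**The direction is unknown.** This stands. A reader might infer that censoring at TPT favours CRP, but that follows only if clinicians select lower-risk patients. The article says only that TPT is at their discretion, and the opposite selection reverses the shift.

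**Clinic staff are blinded, and the analysis plan may add more.** Blinding makes equal shares more plausible. It does not guarantee them, since planned 3HP initiation is 55% against at most 15%. The analysis plan is not shown, so the absence of a weighting model is no fault. The point concerns the rule that the article does fix.

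**Conclusion.** The concern holds in limited form. The rule treats a marker of the outcome as if it were a co-intervention. Censoring there is likely informative, discards deaths, and leaves unclear what happens to baseline-detected cases. As a result, none of the analyses stated in the article shows whether the result depends on TB treated without confirmation after month 3.

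The size cannot be determined from the article. The hazard ratios of 0.75 and 0.55 against 0.64 illustrate assumed unequal shares; with equal shares all versions agree and only power falls (0.80 to 0.77–0.68 for shares of 10–40%). The documents do not support saying that the primary result is biased, or that the bias favours either arm. This is a change worth making to a sensitivity analysis, not a flaw in the primary analysis.

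**What to change.** Keep the primary endpoint and analysis. Then:

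1. Limit the censoring sensitivity analysis to clinician-started TPT. Inverse-probability-of-censoring weights using baseline CD4, site and screening result would be a useful option.
2. State that treatment of baseline-detected TB is not a co-intervention, and do not censor deaths at TB treatment.
3. Add a sensitivity composite in which TB treatment started after month 3 for any reason, in participants without prevalent TB, counts as incident TB alongside confirmed TB and death. Report by arm the number treated with and without confirmation.

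The cost is wording and code. Clinician-started TB treatment and TPT are already extracted at follow-up (Medical record review), so no visits or specimens are added. The changes should be fixed before any unblinded analysis. The drawback is that some empiric treatment will be for non-TB illness, possibly unequally by arm. The added composite should therefore be read beside the primary result, not in place of it.

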**C. TPT uptake**		
Number screen-negatives prescribed TPT	# screen-negatives prescribed TPT (baseline screen-negatives prescribed TPT ~ study staff-prescribed TPT)	None
Proportion screen-negatives prescribed TPT	# screen-negatives prescribed TPT	# randomized to corresponding study arm
Number screen-positives prescribed TPT	# screen-positives prescribed TPT (baseline screen-positives prescribed TPT ~ routine clinician-prescribed TPT)	None
Proportion screen-positives prescribed TPT	# screen-positives prescribed TPT	# randomized to corresponding study arm
Number initiated on TPT	# screen-negatives prescribed TPT + # screen-positives prescribed TPT	None
Proportion initiated on TPT	# screen-negatives prescribed TPT + # screen-positives prescribed TPT	# randomized to corresponding study arm
Time to TPT initiation	Days from baseline TB screening to initiation of TPT	
Number completing TPT (measured by pill count, self-reported adherence)	# initiated on TPT who completed ≥90% of treatment over prescribed TPT period	None
Proportion completing TPT (measured by pill count, self-reported adherence)	# initiated on TPT who completed ≥90% of treatment over prescribed TPT period	# randomized to corresponding study arm

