### Sample size

The sample size calculations are primarily based on the primary objective (which requires a larger sample size). We expect 2-year mortality of 5.2% and 2-year TB incidence of 7.3% in the control arm [4, 28]. Assuming a two-sided alpha of 0.05 and 12% lost to follow-up, a sample size of 860 participants per arm (1720 total) will provide 80% power to detect a relative reduction of 35% in the 2-year combined outcome (from 12.5% [*n* = 95] to 8.1% [*n* = 62]). This sample size will also provide 85% and 90% power if 2-year mortality is 6.8% and 8.8%, respectively (Table 3). This sample size also gives 80% power to detect a smaller 29% relative reduction if the 2-year combined TB incidence and mortality in the control arm is as high as 17.5% with a 10% loss to follow-up. We will analyze the primary outcome as time-to-event and therefore expect this study power assuming binary outcomes will be a lower bound for study power.

**Table 3 Tab3:** Power calculations (power to detect 35% difference in the combined 2-year TB incidence and mortality outcome when 2-year TB incidence is 7.3%)

2-year mortality		Power
POC CRP-based screening	Symptom-based screening	
3.4%	5.2%	0.80
4.4%	6.8%	0.85
5.1%	7.9%	0.88
5.7%	8.8%	0.90

For the secondary objective, based on published estimates of specificity from similar settings, we estimate no more than 15% of all patients in the control arm will initiate 3HP (and 13.5%, or 90% of all control patients initiating 3HP, will complete 3HP) [16, 17, 20]. This sample size will give more than 90% power to show improvements in the proportion of all patients initiating 3HP by an absolute difference of 6% of more, which is much less than what is considered clinically important; we anticipate 55% of all patients in the POC CRP will initiate 3HP (and 55% of all patients will complete 3HP).

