#### TPT and TB treatment adherence monitoring

For participants receiving 3HP, we will assess adherence by performing pill counts and patient-reported adherence. In addition, we will review the medical record and record the number of 3HP refill visits completed. For participants receiving active TB treatment, we will review clinic TB treatment records and record the number of treatment months recorded as complete.

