To evaluate intermediate outcomes on the pathway to the composite primary trial outcome, we will determine the proportion of randomized participants initiating TPT (prescribed TPT), the proportion of randomized participants completing TPT (≥90% TPT pills taken), the proportion of randomized participants diagnosed with prevalent TB, and the proportion of randomized participants with prevalent TB completing TB treatment (by clinic record review). The primary analysis will be by ITT, with the outcome of initiating any TPT based on actual events, irrespective of whether the algorithm was followed. Participants eligible for 3HP based on the results of baseline screening (i.e., study-initiated TPT) may decline to initiate 3HP after randomization despite being prescribed 3HP; these participants will be counted as not having started TPT. Participants who were initiated on TPT during study follow-up (i.e., clinician-initiated TPT for participants who were classified as ineligible for 3HP based on the results of baseline screening) will be counted as having started TPT; 6 months of daily isoniazid (IPT) is currently the most common TPT regimen available for routine clinical use. We will compare the proportion of PLHIV initiating any TPT (study- and clinician-initiated TPT) and the proportion of PLHIV completing TPT (the denominator will be the total number of participants in the study arm), calculating the risk difference and 95% confidence intervals (CI) using standard methods, adjusted for study site using Cochran-Mantel-Haenzsel weights. If respective data on an outcome is missing or a patient is lost to follow-up, it will be assumed that the patient did not initiate nor complete TPT (depending on what data are available). Our working hypothesis is that POC CRP-based TB screening will increase the proportion of PLHIV initiating and completing TPT by at least 40%, relative to symptom-based screening. We will compare the proportion of PLHIV with screen-positive prevalent TB and the proportion of PLHIV with screen-positive prevalent TB completing TB treatment, calculating the risk difference and 95% CIs using standard methods, adjusted for study site using Cochran-Mantel-Haenszel weights. Our working hypothesis is that the proportion of PLHIV with screen-positive prevalent TB will be similar in each arm, and we expect the upper bound of the CI of the difference will be no more than 5%. We consider this margin of 5% sufficiently small to conclude equivalence.

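### TPT initiation is defined as prescription in Table 2 but as actual start in the analysis text, so the size of the uptake difference depends on which definition is used

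*Protocol article*

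**What the plan says.** **Initiation.** Table 2, part C, builds both the number and the proportion initiated on TPT from "screen-negatives prescribed TPT + # screen-positives prescribed TPT". The Statistical methods text (Primary and secondary outcomes) lists among the intermediate outcomes "the proportion of randomized participants initiating TPT (prescribed TPT"), which is the same equation. Two sentences later it describes an intention-to-treat analysis "with the outcome of initiating any TPT based on actual events, irrespective of whether the algorithm was followed". It then says that participants eligible for study 3HP "may decline to initiate 3HP after randomization despite being prescribed 3HP; these participants will be counted as not having started TPT". Clinician-initiated TPT counts as started, and the comparison pools both sources: "We will compare the proportion of PLHIV initiating any TPT (study- and clinician-initiated TPT").

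**Completion.** Table 2 defines completion as at least 90% of treatment among those initiated on any TPT, by pill count and self-report, over all randomized. The adherence section says: "For participants receiving 3HP, we will assess adherence by performing pill counts and patient-reported adherence", and adds a count of 3HP refill visits. Table 1 places TPT adherence monitoring under screen-negatives, at week 6 and month 3. The Participant timeline gives extra adherence visits to patients on 3HP or TB treatment. When data are missing or a participant is lost, "it will be assumed that the patient did not initiate nor complete TPT".

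**Planning.** The Sample size section has 15% of control starting 3HP and 13.5% completing it, which is 90% of starters. For the CRP arm it has 55% starting "and 55% of all patients will complete 3HP".

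**The concern.** The two initiation rules give different answers for the same person, and a later analysis could follow either one and still claim to match the protocol. The choice is not neutral. Study prescriptions go to screen-negatives, and the plan expects far more of these in the CRP arm. They are issued by study staff who know the allocation, so a prescription count comes close to restating the screening result. Initiation also feeds the time-to-initiation row and the completion numerator in Table 2, and is among the items reported to the DMC.

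For completion, participants who screen positive but test negative can get TPT only from treating clinicians, usually as six months of isoniazid. No adherence procedure is described for that route. If such completions go unrecorded and are scored as failures, more of them would be lost in the control arm, which is expected to have more screen-positives.

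**Working it through.** **1. The plan's own figure.** Inputs from Sample size: 15% in control, a 6-point difference (so 21%), 860 per arm, two-sided 0.05, more than 90% power. Normal approximation with pooled variance under the null, mean proportion 0.18:

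- 0.06 × √860 = 1.760
- 1.96 × √(2 × 0.18 × 0.82) = 1.065
- √(0.15 × 0.85 + 0.21 × 0.79) = 0.542
- z = (1.760 − 1.065) / 0.542 = 1.28, so power = 0.900

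The stated power reproduces and is not in question.

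**2. Initiation: prescription against start.** Assume that the planned 55% and 15% are prescribed study 3HP and that a share d declines in each arm. The protocol gives no value for d.

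- Prescription count: 55 − 15 = 40 points
- Actual-start count: 40 × (1 − d)
- Excess from counting prescriptions: 40 × d

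| d | Actual-start difference | Excess under Table 2 |
|---|---|---|
| 5% | 38 | 2 |
| 10% | 36 | 4 |
| 20% | 32 | 8 |
| 30% | 28 | 12 |

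With unequal decline the excess is 55 × d(CRP) − 15 × d(control). Clinician-prescribed TPT is left out of this sum. Unfilled clinician prescriptions, if more common in control, would reduce the excess.

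**3. Initiation: missing scored as not initiated.** With an equal 12% loss (the loss assumed in Sample size), the 40-point difference becomes 40 × 0.88 = 35.2. This moves away from CRP.

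**4. Completion.** Assumptions: 90% completion of 3HP in both arms; 10% prevalent TB per arm, which cancels; a share c of the remaining screen-positives gets clinician TPT; a share k of these complete; and none of that completion is recorded, which is the worst case.

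- Remaining screen-positives: control 100 − 15 − 10 = 75%; CRP 100 − 55 − 10 = 35%
- Measured difference: 0.9 × (55 − 15) = 36 points
- True difference: 36 − (75 − 35) × c × k

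| c | True difference, k = 50% to 90% | Tilt toward CRP |
|---|---|---|
| 10% | 34.0 to 32.4 | 2.0 to 3.6 |
| 30% | 30.0 to 25.2 | 6.0 to 10.8 |
| 50% | 26.0 to 18.0 | 10.0 to 18.0 |

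The protocol gives neither c nor k, nor the share unrecorded.

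**5. Planned completion.** Control: 13.5 / 15 = 90%. CRP: 55 / 55 = 100%. At 90%, 55% starting would give 49.5% completing. Equally, 55% completing at 90% would need 55 / 0.9 = 61.1% starting.

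**The case against.** A reader might infer that both uptake results are tilted toward CRP. The document does not support this for initiation. The decliner rule takes successes away from the arm with more prescriptions, which is CRP. Clinician starts count in both arms, and equal loss scored as failure shrinks the difference. Initiation tilts only if the Table 2 count prevails.

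A reader might also infer that completion is measured only in 3HP takers. The article does not say so. The Table 2 numerator covers any regimen, interviews and record extraction run to month 24, and extraction picks up clinician-initiated TPT as a new medication. That adherence is assessed only for 3HP is inferred from what the adherence section, Table 1 and the Participant timeline describe. A condensed article may leave the isoniazid procedure to the full protocol. What stands is that the procedures it does describe stop at 3HP while the outcome does not.

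Nor can 49.5% be called the correct CRP completion figure, since the starting proportion could be the wrong input instead. A 36-point completion contrast is not shown to miss the working hypothesis either. That hypothesis is an increase of at least 40% relative to symptom screening, which 49.5% against 13.5% far exceeds if read as a relative increase, and it is not a success criterion.

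Finally, these are intermediate outcomes, and the planned 40-point initiation gap is far above the 6-point detectable difference. That stands and limits the severity.

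**Conclusion.** The contradiction over initiation is established from the text alone, both between Table 2 and the analysis section and within that section. Its effect, if Table 2 is followed, is 40 points times the decline rate, given equal decline and the planned 55% and 15% read as prescriptions. Under the actual-start rule there is no such tilt.

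The completion point is conditional. Any unrecorded completion of clinician-initiated TPT would fall mostly in control and favour CRP, by an amount the protocol cannot fix. Even the largest illustrative tilt of 18 points leaves a true difference of 18 points in favour of CRP.

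The 55%/55% planning figure is inconsistent with 90% completion in control, but no stated power rests on it. The primary endpoint and the power for initiation are untouched. This is a moderate issue about how large the reported uptake effect will be, not one that must be resolved before the trial can be interpreted.

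**What to change.** 1. In Table 2 and in the Statistical methods text, define initiated on TPT as a recorded actual start (first dose or dispensing) of any study- or clinician-initiated TPT, in both arms. Remove the equation with prescription. Keep the existing Table 2 rows for TPT prescribed to screen-negatives and screen-positives as separate process measures. This costs wording only; the expected initiation difference may be somewhat smaller.
2. State how completion is recorded for clinician-initiated TPT. The refill review is described for 3HP only, so extend it to clinician-initiated regimens, whose starts are already extracted, and use that same source for completion in both arms. Pill count and self-report can stay as supporting data for 3HP. The cost is modest extra data extraction.
3. Reconcile the starting and completing proportions for the CRP arm in Sample size, or state why completion among starters is expected to be 100% there and 90% in control. No recalculation of power is needed.
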